### Data collection and management

Initially, the screening personnel reviewed the inclusion and exclusion criteria and collected basic characteristic data prior to random allocation. Trained assessors, who are blinded to the allocation and not involved in the intervention, will play a crucial role in measuring the primary and secondary outcomes. The data for all participants will be recorded in a designed case report form (CRF). Additionally, each CRF will be checked twice to ensure the accuracy and completeness of the data collection throughout the study. All relevant documents will be coded with specific identification numbers and kept in a secure, locked box to safeguard the privacy and data safety of the subjects. The magnetic resonance scans obtained during the study will be saved on a computer with restricted access and a password known only to the principal investigator. The materials will be securely stored in compliance with medical records retention regulations and good clinical practice principles for 5 years after the trial. The study will also be monitored for safety by a physical therapist and two clinical doctors who are not involved in the research. The researchers will ensure that the study is conducted in compliance with standard operating procedures (SOPs), monitor the study’s progress, review all adverse events, and discontinue the trial if any measures cause significant adverse effects such as headache, nausea, or vomiting. The assessors reported any adverse events to the *data monitoring committee* (DMC) and the ethics committee of Yueyang Integrated Chinese and Western Medicine Hospital affiliated with Shanghai University of Traditional Chinese Medicine. DMC is independent from the sponsor and competing interests.

### Statistical analysis

All nonimaging data will be analysed using SPSS version 21 by an independent statistician who is blinded to the treatment and control groups to ensure objectivity and reduce bias. The statistical significance level for testing will be set at 0.05 with a two-tailed test. Continuous variables are presented as the mean, standard deviation, or maximum or minimum values based on their statistical distributions. Independent sample *t* tests or nonparametric tests (Mann–Whitney *U* test) will be used to compare the results presented as continuous variables and mean values to validate the effectiveness of the intervention. Furthermore, intra- and intergroup comparisons were made at 4 weeks to observe the differences between the two intervention methods. If necessary, logistic regression, general linear correlation, or regression was used to compare different types of results based on the variable type and distribution. Basic data comparisons between the treatment and control groups will be performed using *t* tests, chi-square tests, or nonparametric tests. Participants who drop out during the intervention period will not be excluded according to the intention-to-treat principle, and missing data will be replaced using the last observation carried forward method to maintain statistical power and avoid bias.

The amplitude of low-frequency fluctuation (ALFF) is an indicator of the amplitude energy of the low-frequency spectrum and reflects the spontaneous activity of neurons in the resting state of the brain. The ALFF is a useful tool for analysing functional MRI data to study longitudinal neural changes and explore the relationship between brain plasticity and the recovery of sensory and motor function induced by stimulation [22]. In this study, the REST 1.9 software from Beijing Normal University (http://www.restfmri.net/) was used to perform linear drift and calculate the amplitude of signal oscillation in each voxel in the low-frequency range (0.01–0.1 Hz) to obtain ALFF images. Finally, the ALFF values of each participant were *Z*-transformed for further statistical analysis.

Longitudinal measurements in a resting-state task and further correlation analysis of imaging and scale score data obtained from baseline and postintervention measurements were performed to explore the relationships between brain remodelling and postoperative sensory and motor function recovery in CSM patients.

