### Participants

The aim of this study was to recruit 78 patients who underwent surgery for CSM, with JOA scores between 5 and 15 and aged between 20 and 75 years. All eligible participants will be recruited from the orthopaedic and rehabilitation medicine departments of our hospital and other hospitals. The study was conducted at multiple centres, including Shanghai Longhua Hospital, Affiliated with Shanghai University of Traditional Chinese Medicine, and Shanghai Shuguang Hospital, Affiliated with Shanghai University of Traditional Chinese Medicine. Both of these hospitals are located in Shanghai, China. Prior to the experiment, we provided a comprehensive explanation of the study’s purpose, type of intervention, and potential risks and benefits of using VR technology to the participants who consented to participate. We will respect their decision to withdraw from the study at any time for any reason. At the same time, we maintained regular contact with participants, created incentives, provided personalised designs, simplified experiment procedures, and increased communication and engagement to increase loyalty and participation and to ensure that the experiment would be successful.

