## Enrolment

### Inclusion criteria

All participants who met the following criteria were included: (1) diagnosed with CSM and underwent surgery between 24 h and 3 months prior to enrolment; (2) aged between 20 and 75 years of either sex; (3) a Japanese Orthopaedic Association (JOA) score of 5 to 15; (4) no less than a primary school education; (5) no cognitive dysfunction; and (6) understood the study, agreed to participate in the study, and signed the informed consent form.

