#### Primary outcome measurement

The primary outcome measure was the change in the JOA score for the cervical spine. The JOA score consists of a total of 17 points, with 4 points each for upper and lower limb motor function, 2 points each for upper and lower limb and trunk sensation, and 3 points each for bladder function. Patients were assessed using the JOA score before intervention, after intervention, and during follow-up in accordance with the JOA evaluation criteria for cervical spine disease treatment established by the Japanese Orthopaedic Association. The results were categorized into five groups: > 75% excellent, 50–74% good, 20–49% fair, 0–19% no change, and < 0 deterioration.

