### Sample size calculation

The goal of our study was to investigate the effectiveness of VR technology in the rehabilitation of patients with CSM after surgery. Due to a lack of research on the effect of VR technology on the rehabilitation of CSM patients after surgery, we conducted a small-sample pilot study. The sample size was estimated based on the improvement in JOA scores for cervical spondylosis reported by the Japanese Orthopaedic Association. One month after surgery, the average JOA scores and SDs for the VR rehabilitation intervention group (*n* = 10) and the conventional rehabilitation group (*n* = 10) were 15.30 (SD = 0.90) and 14.7 (SD = 0.78), respectively, with an effect size (Cohen’s *D*) of 0.71. Using the Gpower 3.1 software, we calculated the needed sample size, which, with a type I error of *α* = 0.05 and a type II error of *β* = 0.2, was estimated to be a sample size of *n* = 64. Considering a dropout rate of 20%, 39 participants were needed for each group, for a total of 78 participants. Finally, we randomly allocated the 78 participants into a VR training combined with rehabilitation intervention group and a conventional rehabilitation group, each consisting of 39 participants.

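### The primary comparison of JOA change ignores baseline JOA; a prespecified ANCOVA would be at least as precise, by an amount the protocol does not let one fix

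*Protocol article*

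**What the plan says.** Under Primary outcome measurement: "The primary outcome measure was the change in the JOA score for the cervical spine". The Outcomes section has it assessed straight after the 4-week intervention and compared with baseline.

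Under Statistical analysis, the between-group method for continuous outcomes is an independent-samples t test or a Mann–Whitney U test, which "will be used to compare the results presented as continuous variables and mean values to validate the effectiveness of the intervention". The test is two-sided at 0.05. Logistic or linear regression is mentioned only for use as needed, chosen by variable type and distribution. It has no named covariate and is not tied to the primary outcome. Participants who drop out stay in the analysis, with the last observation carried forward.

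Baseline JOA is available for everyone: the Outcomes section has all participants scored on JOA, VAS and NDI before the intervention, and the Randomization section places allocation after the baseline evaluation. The inclusion criteria admit JOA scores from 5 to 15; Table 1 gives a maximum of 17.

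**The concern.** A patient who enters at 15 can gain at most 17 − 15 = 2 points; one who enters at 5 can gain 17 − 5 = 12. A raw change score carries that baseline spread into its error term, and a t test or rank test does nothing to remove it. Putting baseline JOA in the model as a covariate does remove it, using a measurement that the trial already takes.

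What is at stake is precision. The trial aims at a difference of 0.6 points with about 32 analysable patients per arm, so a wider standard error than necessary lowers the chance of detecting that difference and widens the reported interval. The optional regression does not close the gap, because an adjusted analysis that may or may not be run, with covariates to be chosen later, is not a prespecified primary analysis.

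**Working it through.** **Inputs from the article (Sample size calculation).** Pilot JOA scores one month after surgery: 15.30 (SD 0.90) with VR and 14.7 (SD 0.78) without, n = 10 each, "with an effect size (Cohen’s *D*) of 0.71". Type I error 0.05, two-sided; type II error 0.2; n = 64 before dropout.

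**The plan's own figure.** Difference = 15.30 − 14.7 = 0.60. Pooled SD = √[(0.90² + 0.78²)/2] = 0.842. d = 0.60/0.842 = 0.7125. The noncentral t solution for 80% power is 31.9 per arm, so 32 per arm and 64 in total. The figure is reproduced. It rests on the SD of follow-up scores, whereas the primary outcome is a change.

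**Assumptions, because the article does not give them.** Baseline SD (SDb), 4-week SD (SDp) and their correlation r. Normal scores, complete data, 32 per arm, difference 0.60.

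**Formulas.**
- SD of change = √(SDb² + SDp² − 2·r·SDb·SDp)
- ANCOVA residual SD = SDp·√(1 − r²)
- With equal SDs, the variance ratio ANCOVA/change is (1 − r²)/[2(1 − r)] = (1 + r)/2

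**Results (power by noncentral t).**

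| SDb | SDp | r | SD change | SD ANCOVA | Variance ratio | Power, change | Power, ANCOVA |
|---|---|---|---|---|---|---|---|
| 0.842 | 0.842 | 0.3 | 0.996 | 0.803 | 0.65 | 66% | 84% |
| 0.842 | 0.842 | 0.5 | 0.842 | 0.729 | 0.75 | 80% | 90% |
| 0.842 | 0.842 | 0.7 | 0.652 | 0.601 | 0.85 | 95% | 97.5% |
| 1.5 | 1.5 | 0.5 | 1.500 | 1.299 | 0.75 | 35% | 44% |
| 2.0 | 2.0 | 0.5 | 2.000 | 1.732 | 0.75 | 22% | 28% |
| 1.5 | 0.842 | 0.5 | 1.302 | 0.729 | 0.31 | 44% | 90% |
| 2.0 | 0.842 | 0.5 | 1.739 | 0.729 | 0.18 | 27% | 90% |

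The second row is the only equal-SD row in which the change-score analysis has the 80% power that the article claims: with equal SDs, the SD of change equals 0.842 only at r = 0.5.

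**Effect of the planned imputation.** The article lists no JOA assessment between baseline and 4 weeks, so for a patient lost before then the carried-forward value is the baseline score. Simulating the last row with 39 per arm, 20% random dropout, 4-week means at the pilot values and assumed baseline means of 11 to 13 gives about 16–21% power for change and 22–43% for ANCOVA. ANCOVA remains ahead, but most of its apparent advantage goes.

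**Cost of a covariate.** At N = 64, estimating one slope inflates the variance by about 1/(64 − 4) = 1.7%.

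**The case against.** The strongest reply is that an unadjusted test keeps its type I error in a randomised trial, that this trial calls itself exploratory, and that a condensed article may leave covariates to a fuller document. The first two parts stand: this is a matter of efficiency, not validity. The third does not dispose of the point, because the article does not leave the method open; it names the test.

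Four stronger readings are tempting, and the documents do not support them.

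- **That the gain is large.** The contrast of 27% with 90% pairs an assumed baseline SD of 2.0 with the pilot SD of 0.84. The wide entry range and pilot means near 15 make that pairing plausible but do not establish it. If a broad entry range also widens the 4-week scores, ANCOVA helps only modestly (22% against 28%).
- **That chance imbalance biases the result.** At baseline SD 2.0, one standard error of imbalance is 2.0·√(2/32) = 0.5 points. With slope 0.5·0.842/2.0 = 0.21, it moves the change difference by 0.5·(1 − 0.21) ≈ 0.4 points. That movement is already part of the SD of change of 1.74; counting it as a separate harm would count it twice.
- **That time since surgery and centre are collected and ready to use.** The article says that patients "underwent surgery between 24 h and 3 months prior to enrolment" and that "The study was conducted at multiple centres". The first is an eligibility window and the second describes the setting. Neither appears in the listed baseline data, although both are probably obtainable, and nothing in the article quantifies a gain from adjusting for them.
- **That missing strata are a fault.** Stratification factors are a detail that an article may omit.

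**Conclusion.** The point holds as one of precision. The article fixes an unadjusted test for the primary outcome although baseline JOA is measured in everyone before allocation. Baseline-adjusted ANCOVA was more powerful in every scenario tried, and in large samples it is never less efficient than the unadjusted change score.

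The size is a range. With equal SDs, ANCOVA has 65–85% of the change-score variance for r from 0.3 to 0.7. The saving is much greater only if baseline JOA varies more than 4-week JOA. All power figures in the table assume 0.6 points, 32 per arm, complete data and normal scores; last-observation imputation would reduce the benefit. This is a worthwhile improvement to the plan and does not make the planned test wrong.

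**What to change.** Make the primary analysis an ANCOVA of 4-week JOA on arm with baseline JOA as covariate. Report the adjusted difference with a 95% confidence interval, using robust or bootstrap standard errors because of the ceiling at 17. Keep the unadjusted t or Mann–Whitney comparison as a sensitivity analysis. Use the same model for VAS and NDI, each with its own baseline. Centre and time since surgery may be added if they are recorded, and should then be named in advance. Revisit the last-observation imputation at the same time, since it would undo much of the gain.

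The cost is an amendment to the analysis wording before the data are unblinded; recruitment was still open when the article was submitted. No new measurement is needed for baseline JOA, and SPSS fits the model. The change is not entirely free: each covariate takes one degree of freedom, and the model assumes a linear relation on a bounded scale, which should be checked.

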### Outcomes

Prior to the intervention, individuals who expressed interest in participating in the study were invited to schedule an appointment for additional information.

If they choose to participate, they will sign an informed consent form and be screened by independent researchers to determine if they meet the inclusion and exclusion criteria. Participants who meet all the inclusion criteria and none of the exclusion criteria will be included in the study. Descriptive data, including general information such as age, sex, race, occupation, height, weight, body mass index (BMI), blood pressure, education level, medical history, medication use, smoking status, drug use, and alcohol consumption, will be carefully collected before randomization. In addition, all participants were assessed using three scales: the JOA, the VAS, and the NDI.

Both the intervention group and the control group completed a total of 12 rehabilitation sessions over a period of 4 weeks. Outcomes will be assessed immediately after the 4-week intervention period and compared with baseline data. The primary outcome will be the change in functional ability, assessed using a standardized functional assessment tool (JOA score). The secondary outcome measures will include pain level (VAS score), neck disability (NDI score), and changes in the functional areas of the brain.

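### The Statistical analysis section lists intragroup pre-post comparisons, unranked beside the between-group ones, as a way to see the difference between the two methods, which they cannot show.

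*Protocol article*

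**What the plan says.** The Statistical analysis section of the protocol article makes two statements in succession. The first names independent-sample t tests or the Mann–Whitney U test, which "will be used to compare the results presented as continuous variables and mean values to validate the effectiveness of the intervention". That is a between-group analysis with a clear efficacy role. The next sentence adds that "intra- and intergroup comparisons were made at 4 weeks to observe the differences between the two intervention methods". It puts the two kinds of comparison side by side under one purpose, does not describe the intragroup ones as descriptive, and states no order between them. The general level in the same section, "The statistical significance level for testing will be set at 0.05 with a two-tailed test", carries no exception for them.

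The Outcomes section shows what an intragroup comparison is here: "Outcomes will be assessed immediately after the 4-week intervention period and compared with baseline data". It is a pre-post comparison. The primary outcome is a change score: "The primary outcome measure was the change in the JOA score for the cervical spine".

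Two further statements describe the patients and their treatment. The Inclusion criteria admit patients "diagnosed with CSM and underwent surgery between 24 h and 3 months prior to enrolment". The Outcomes section says: "Both the intervention group and the control group completed a total of 12 rehabilitation sessions over a period of 4 weeks".

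**The concern.** A change from baseline within the VR arm contains any VR effect, but also recovery after decompression, the conventional rehabilitation that both arms receive, and regression to the mean. Patients enter as early as 24 hours after the operation, so improvement in both arms is to be expected even if VR adds nothing. A significant change in one arm beside a non-significant change in the other is not a test of the difference between them either: the two p-values can fall on opposite sides of 0.05 by chance.

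Only the randomised contrast separates VR from what is common to both arms. If the intergroup test were not significant, the sentence as worded would still let an intragroup result be cited as showing a difference between the methods.

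**Working it through.** **1. What the plan's own sample size is built on.** Inputs from the Sample size calculation section: pilot JOA means 15.30 (SD 0.90) and 14.7 (SD 0.78), α = 0.05, β = 0.2.

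- Pooled SD = √[(0.90² + 0.78²)/2] = 0.842.
- d = (15.30 − 14.7)/0.842 = 0.712, which agrees with the stated 0.71.
- A two-sided two-sample t test with 32 per arm has 80.1% power at d = 0.712. This reproduces the stated total of 64.
- Planned enrolment after the dropout allowance is 39 per arm.

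The trial is therefore sized for a between-group comparison.

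**2. What happens if pre-post results are read as showing a difference.** Assume no VR effect, so that both arms have the same true mean change. Let dz be that change divided by the SD of change. The protocol gives neither an expected change nor an SD of change (the pilot figures are scores at one month, not changes), so dz is an assumption and is varied. Changes are taken as normal and the arms as independent.

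For a paired t test in one arm of n patients at two-sided 0.05:

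- p = P(T > t₀.₉₇₅,ₙ₋₁), where T is noncentral t with n − 1 degrees of freedom and noncentrality dz·√n.
- P(VR arm improves significantly, control arm does not) = p(1 − p).

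With n = 39, √39 = 6.245 and the critical value is 2.024:

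| dz | dz·√39 | p (VR arm significant) | p(1 − p) (VR only) |
|---|---|---|---|
| 0 | 0 | 2.5% | 2.4% |
| 0.2 | 1.249 | 22.9% | 17.7% |
| 0.3 | 1.873 | 44.7% | 24.7% |
| 0.4 | 2.498 | 68.2% | 21.7% |
| 0.5 | 3.122 | 86.1% | 12.0% |
| 0.8 | 4.996 | 99.8% | 0.2% |

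Example at dz = 0.3: 0.4468 × (1 − 0.4468) = 0.247. Since p(1 − p) cannot exceed 0.25, 25% is the ceiling; with 39 per arm it is reached near dz = 0.32.

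With 32 per arm, the VR-only figures at dz = 0.3, 0.4, 0.5 and 0.8 are 23.5%, 24.2%, 17.0% and 0.8%, so the picture is the same.

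The control-only pattern is equally likely under these assumptions but could not be mistaken for a VR benefit, so it is left out.

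**3. The between-group test under the same conditions.** In 50,000 simulated trials per setting (n = 32 and 39; dz = 0, 0.2, 0.35, 0.5, 0.8 and 1.0), the two-sample t test on change rejected in 4.8% to 5.2% of trials, and in about 2.5% in favour of VR. The recovery common to both arms cancels, so its size does not matter.

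**The case against.** The strongest reply is that the efficacy test is already between-arm. The sentence immediately before the quoted one gives the t test or Mann–Whitney U the job of validating effectiveness. The quoted sentence only adds to it and speaks of observing. Elsewhere the document points the same way. The Abstract aims at differences between the intervention and control groups and ties intragroup brain changes to a separate correlation question. The section on unblinding speaks of significance between treatment and control. The sample size rests on a between-group effect. The sentence can also be read jointly, as covering two kinds of comparison of which one does compare the methods. Finally, the study calls itself exploratory, and precedence among analyses is often left to the SAP, which is not shown.

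Most of this stands, and it limits the point. A reader might infer that the trial will judge VR by within-arm tests, that the protection of randomisation is lost, or that the plan's false-positive rate is well above 5%. The documents do not support that. A valid between-group test is planned, and nowhere is a significant VR-arm change, or significance in the VR arm only, adopted as a decision rule. The percentages above describe a reading that the sentence allows, not the error rate of the stated plan.

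It is also fair that the VR-only pattern becomes rare if recovery is large. The remaining hazard is then a different one: taking the VR arm's own improvement as evidence for VR.

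What the reply does not remove is the sentence itself. It assigns a purpose to intragroup comparisons that they cannot serve. That is a stated purpose that is wrong, not a detail left to the SAP.

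**Conclusion.** The point holds as a wording error with a real but conditional consequence. The planned between-group test is sound and keeps its error rate. The added sentence offers intragroup comparisons, unranked and not labelled descriptive, as a second way of seeing a difference between methods.

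If they were read so with no true VR effect and 39 per arm, significance in the VR arm only would appear in about 25%, 22% and 12% of trials at a common standardized change of 0.3, 0.4 and 0.5, against about 2.5% in favour of VR for the between-group test. At its peak that is about ten times as often (25/2.5). At 0.8 the pattern falls to about 0.2%, but the VR arm's own improvement would be significant in 99.8% of trials. These figures rest on assumed standardized changes, normal changes and full follow-up of 39 per arm; at 32 per arm the conclusion is the same. The correction is worth making because it closes an invalid route to a claim at no cost.

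**What to change.** Reword the second sentence in the Statistical analysis section to say that:

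- the difference between the two methods is judged only by the between-arm difference in change from baseline to 4 weeks, with its 95% CI, for JOA and likewise for VAS and NDI;
- within-arm changes are reported descriptively, for example as mean change with CI, and are not evidence of a VR effect.

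Leaving out within-arm p-values would be the cleaner presentation, but the essential step is the descriptive label.

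The cost is wording only. No new data, patients or analyses are needed, and neither the planned between-group test nor the sample size changes. Recruitment was still under way at submission, and the Protocol amendments section provides the route.

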### Withdrawal or dropout criteria

In this study, the intervention measures for both the trial group and the control group may be stopped if the subject meets any of the following criteria: (1) the subject requests to withdraw from the clinical study; (2) the subject is unable to complete the relevant test as needed, which affects the data collection; (3) the subject receives other treatments during the treatment period without authorization; (4) the subject experiences adverse events or serious adverse events during the trial that require their withdrawal from the study; (5) the subject experiences significant worsening of the disease, complications or special physiological changes that require their withdrawal from the study; (6) the researcher considers it unsuitable for the subject to continue participating in this study.

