#### Neuroimaging scans

The data for this study were collected at the Radiology Department of Yueyang Hospital of Integrated Traditional Chinese and Western Medicine, which is affiliated with the Shanghai University of Traditional Chinese Medicine. Participants were positioned in the supine position, and their heads were secured using a specially designed head mask. All magnetic resonance imaging (MRI) scans were performed using a Siemens Magnetom Verio 3. T MRI scanner. Resting-state functional MRI (fMRI) data were obtained using a single-shot echo-planar imaging (EPI) sequence with interleaved scanning of 43 slices, a flip angle of 90°, a matrix of 64 × 64, a TR of 300 ms, a slice thickness of 3.0 mm, an FOV of 230 × 230 mm^2^, and a gap of (voxel size of 3.6 × 3.6 × 3.0 mm^3^). T1-weighted structural scans were obtained using a weighted fast spoiled gradient-echo (FSPGR) sequence with TR/TI/TE of 190/900/2.93 ms, a flip angle of 9°, an FOV of 256 × 256 mm^2^, a slice thickness of 1.0 mm, a matrix of 256 × 256, and an average of 1.0. All assessments involving scales and MRI scans were conducted prior to the intervention and then repeated after 4 weeks of intervention.

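### With scales taken only at baseline and week 4, last observation carried forward sets the JOA change to 0 for anyone without a week-4 value, so it neither protects power nor avoids bias as the plan claims

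*Protocol article*

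**What the plan says.** The primary endpoint is a change score: "The primary outcome measure was the change in the JOA score for the cervical spine". The rule for absent values stands under Statistical analysis: "missing data will be replaced using the last observation carried forward method to maintain statistical power and avoid bias". The same section keeps early leavers in the comparison: "Participants who drop out during the intervention period will not be excluded according to the intention-to-treat principle". No other primary method for missing data is given.

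The assessment times are fixed elsewhere. Under Outcomes: "Outcomes will be assessed immediately after the 4-week intervention period and compared with baseline data". Under Neuroimaging scans: "All assessments involving scales and MRI scans were conducted prior to the intervention and then repeated after 4 weeks of intervention". Secondary outcome measures gives the same two times. Primary outcome measurement adds one more JOA occasion: "Patients were assessed using the JOA score before intervention, after intervention, and during follow-up". That follow-up has no date and is listed after the post-intervention assessment.

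The Sample size calculation arrives at 64 participants and then states: "Considering a dropout rate of 20%, 39 participants were needed for each group, for a total of 78 participants". One of the Withdrawal or dropout criteria is that "the subject is unable to complete the relevant test as needed, which affects the data collection".

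**The concern.** Carrying the last observation forward needs an observation after baseline. Here there is none before week 4, so for anyone who misses that assessment the rule is baseline carried forward. The imputed JOA change is 0, which falls in the article's own category for no change.

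Zero is not a neutral value in this population. Participants enter between 24 hours and 3 months after surgery, and both arms receive active rehabilitation, so some recovery is expected in each. Imputed zeros pull both arm means down and mix a spike at 0 with the real changes, which widens the spread. If the arms lose different proportions, the pull differs and creates a difference that is not a treatment effect.

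The plan is also inconsistent with its own sample size. The calculation treats the 20% as lost to the analysis, whereas the analysis section brings them back as patients with zero change, for which the calculation makes no allowance.

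**Working it through.** **Inputs from the article.** Pilot JOA one month after surgery: VR 15.30 (SD 0.90), control 14.7 (SD 0.78), 10 per arm. Two-sided α 0.05, power 0.80, 20% dropout, 39 per arm.

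**Assumptions.** The article gives no baseline JOA mean and no SD of change, only the eligibility range 5–15. I therefore take mean control recovery over 4 weeks as 1, 2 or 3 points, and the change SD as 0.84 (the pilot SD of scores, borrowed) or 1.5. Dropouts are assumed to recover like everyone else (missing completely at random).

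**The plan's own figure.** Pooled variance = (0.90² + 0.78²)/2 = 0.7092, so SD = 0.842 and d = 0.60/0.842 = 0.7125. A two-sample t-test with noncentral-t power needs 31.9, so 32 per arm, 64 in total. The stated 64 reproduces. Then 32 × 1.2 = 38.4, rounded up to 39 per arm and 78 in total.

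**Reference power.** After 20% loss, 39 × 0.8 = 31.2 per arm remain. Analysing completers gives 79% power at 31 per arm and 80% at 32.

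**Formula.** With dropout proportion p, true mean change μ and SD σ, the change after imputing zeros has

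- mean (1 − p)μ
- variance (1 − p)(σ² + μ²) − [(1 − p)μ]²

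**Equal dropout of 20%.** The difference is 0.8 × 0.60 = 0.48 whatever the recovery. Worked case, control recovery 2 and VR 2.6, σ² = 0.7092:

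- control variance: 0.8 × 4.7092 − 1.6² = 1.207
- VR variance: 0.8 × 7.4692 − 2.08² = 1.649
- pooled SD: √1.428 = 1.195
- noncentrality: (0.48/1.195) × √(39/2) = 1.77, so power is 42%

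| Control recovery (points) | Power, SD 0.84 | Power, SD 1.5 |
|---|---|---|
| 1 | 62% | 31% |
| 2 | 42% | 25% |
| 3 | 28% | 20% |
| Completers only | 79–80% | 34% |

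The article also allows a Mann–Whitney test. By simulation at SD 0.84 its power on the imputed data is 55%, 48% and 48%. With equal dropout and no true effect, type I error stays at 5%.

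**Unequal dropout, no true effect.** The spurious difference is μ × (control dropout − VR dropout). At SD 0.84, by simulation or the formula above:

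| Dropout in the two arms | Spurious difference (recovery 1, 2, 3) | Type I error |
|---|---|---|
| 25% and 15% | 0.1, 0.2, 0.3 | about 8%, 13%, 16% |
| 30% and 10% | 0.2, 0.4, 0.6 | about 18%, 37%, 47% |

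The sign favours VR if control loses more, and control if VR loses more. The error rate is the same either way.

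**Unequal dropout, true effect 0.6, SD 0.84.** If VR loses 30% and control 10%, the expected difference is 0.7(μ + 0.6) − 0.9μ = 0.42 − 0.2μ, that is 0.22, 0.02 or −0.18. The rejection rate is then 18%, 5% or 8%. If control loses 30% and VR 10%, it is 0.9(μ + 0.6) − 0.7μ = 0.54 + 0.2μ, that is 0.74, 0.94 or 1.14, and the rejection rate is 93–95%.

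**The case against.** The structural point is not in dispute: no section supplies a value between baseline and week 4. The schedule figure is not shown, but three sections agree on two time points, and the undated JOA follow-up comes too late to be carried to week 4. The objections concern reach and size, and most of them stand.

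- A reader might measure the loss from 87%, the power of 39 per arm with no dropout. The article never plans for that. The fair reference is completers, 79–80%; the remaining 7–8 points are the ordinary cost of losing patients.
- The SD of 0.84 describes pilot scores at one month, not changes. At 1.5 the loss attributable to imputation is much smaller, 34% to 31%, 25% or 20%. It does not vanish.
- A reader might infer that the rule always cuts power. It does not. If control loses many more patients, rejection rises to 93–95%. That rise comes from bias, so it is no defence of the method.
- A reader might infer that the rule favours VR. The article gives no dropout by arm. Intolerance of VR could empty one arm and disappointment in an open trial the other; either direction is conjecture.
- A reader might infer that everyone who stops treatment is scored 0. Only those without a week-4 value are. The withdrawal criteria speak first of stopping the intervention, so some who stop may still be assessed.
- The trial calls itself exploratory, and 20% is a planning allowance, not an observed rate. This lowers the stakes but does not make the stated justification true.

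**Conclusion.** The concern holds in this form. For participants without a week-4 assessment the planned rule is baseline carried forward, the imputed JOA change is 0, and the reason given for the rule is wrong on both counts. At the plan's own 20% dropout, equal in both arms, a true difference of 0.6 is estimated as 0.48. Power on the change-score t-test falls below that of simply leaving the dropouts out: 28–62% against 79–80% if the change SD is 0.84, and 20–31% against 34% if it is 1.5. These figures assume control recovery of 1 to 3 points and dropout unrelated to outcome.

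Equal dropout leaves the type I error near 5%, so a false positive result does not follow from the rule alone. Unequal dropout can bias either way. With no true effect and SD 0.84, the spurious difference is 0.1–0.3 points and the error rate about 8–16% at 25% against 15%; at 30% against 10% they are 0.2–0.6 points and about 18–47%. The document supports no prediction of which arm would gain.

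**What to change.** In Statistical analysis, replace last observation carried forward as the primary method with a likelihood-based analysis or multiple imputation that uses baseline JOA and the other baseline data already collected. Keep baseline carried forward only as a sensitivity analysis labelled as such, and delete the clause claiming that it protects power and avoids bias. State that participants who stop the intervention are still asked to attend the scheduled week-4 JOA assessment unless they withdraw consent for follow-up; observed values help more than any imputation. The handling of the 20% in the sample size section then agrees better with the analysis.

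The cost is an amendment to the text, a little more analysis, and some effort to bring stopped patients to one visit already on the schedule. The change should be made before anyone sees results by arm.
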